### Assessments

All patients have been medically examined prior to referral and somatic explanations for the fatigue will be ruled out either at the outpatient clinic of the department of internal medicine of the Radboud university medical center or by the referring general practitioner. The baseline assessment consists of two intake sessions and two test sessions at our treatment centre. Questionnaires are completed during both test sessions. Between test sessions, patients will wear an actometer and register their activities and symptoms in a diary. The actometer is a motion-sensing device worn at the ankle for 12 consecutive days and nights [18]. Trained cognitive behavioural therapists will perform the intake. They are all psychologists specialized in treating patients with CBT for CFS. During the first intake session with a therapist the Mini International Neuropsychiatric Interview (MINI) will be completed to assess the presence of psychiatric disorders [19]. At the half-year post randomization assessment, patients fill in the same questionnaires as at T0. Patients will also wear the actometer again and complete the diary. After randomization patients will receive a letter with the second assessment date and the face-to-face session with their therapist for evaluation of the web-based intervention or start of treatment for the wait list controls. Patients will receive reminders when questionnaires are not completed within one week. When patients do not want an evaluation session, the researcher will contact the patient with the request to complete the assessment as previously agreed. When a patient does not want to complete the full assessment, he or she will be requested to only fill in the questionnaire that assess the primary outcome measure.

We did not use a data monitoring committee for this study. All data will be monitored by a data-manager of the department who is not part of the research team. All participants have a study number in the data file. The file connecting study numbers with identifying personal data is separately stored and protected with a password that is only known to the principal investigator. All authors will have access to the final dataset.

### Intervention

Both web-based CBT interventions have a maximum duration of six months. All patients will receive a private username and password, ensuring private communication with their therapist. After patients accept the general terms of the web-based treatment, patients will get their unique username and password (by email) necessary for logging in on the portal.

The web-based CBT is based on the protocol for face-to-face CBT for CFS [8]. The protocol consists of several modules or subparts (see Table 2).

**Table 2 Tab2:** Module titles and specific subparts of the web-based CBT for patients with CFS

Module title	Content of module
Getting started and goal setting	Psycho education about the cognitive-behavioural model of CFS and CBT, signing treatment contract and establish goals that if attained implies that a patient no longer has CFS.
Regulate sleep-wake cycle	Regulating sleep-wake cycle i.e., fixed bedtimes, no sleeping or lying down during the day
Helpful beliefs about fatigue	Formulate helpful beliefs
	Divert attention away from fatigue towards other activities and the environment
How to communicate with others about CFS	Change the communication about CFS with significant others
Gradually increasing my activities	Determine activity pattern
	Graded activity program for relative active patients (first spread activities evenly, followed by graded activity)
	Graded activity program for low active patient
	Pain: helpful beliefs for dealing with pain during graded activity
	Solve problems with the graded activity program
Reaching my goals step by step	Work resumption
	Increase mental activities
	Increase social activities
	Achieve my goals step by step
Evaluation and the future	Letting go of the rules of therapy (e.g., sleep in late, do a lot of activities from time to time)
	No longer being a CFS patient
	Having healthy levels of fatigue and learn how to stay healthy

After completion of the first *Getting started and goal setting*-module, the following modules—from ‘*Regulate sleep-wake cycle’* to ‘*Reaching my goals step by step’*—will be available to the patient. After completion of the sixth module, the last module ‘*Evaluation and the future’* will be available. Patients can send emails and have chat sessions with their therapists. Patients can also view interview excerpts with recovered CFS patients who share their experiences with web-based CBT. In these excerpts, patients explain the different elements of the treatment and talk about their experience with the intervention. Patients can print all texts and assignments. During development of the intervention, before the start of the study, seven patients were asked to evaluate the usability of the intervention. The think aloud method [20] was used in this pilot and improvements have been made to the Internet program. Three out of these seven patients were interviewed. Excerpts of these interviews were reported in this trial paper. After the pilot study, the intervention will only be available to patients participating in the study and allocated to one of the treatment arms. Therapists have access to the assignments and registration forms that are filled in by patients. In a box at the bottom of each completed assignment therapists can give feedback. In both conditions the therapist will respond within five working days after the patient sent an email. When practical problems with the program occur or when communication between therapist and patient is not sufficient to resolve a specific problem via email or by chatting, telephone contact will be offered to the patient. All data of patients—i.e., assignment, forms, and communications with the therapist—will be encrypted and securely stored on the mainframe of the Internet portal supplier.

#### Low active versus relative active

With data from the actometer, two activity patterns can be discerned: a low activity pattern and a relatively active pattern. The individuals' activity patterns will be based on the 12 daily physical activity scores (van der Werf, Prins, Vercoulen, van der Meer, & Bleijenberg, 2000). Two physical activity patterns can be discerned. The average daily physical activity scores of low active patients stay below the general mean physical activity of CFS patients in at least 11 of 12 days. Relative active patients score at least 2 of 12 days above the mean physical activity score of CFS patients. Relative active patients have fluctuating activity levels with bursts of activity followed by (prolonged) periods of rest [18]. In case of missing actometer data at baseline, therapists will determine the activity pattern by using a structured interview [21].

In accordance with the CBT protocol for face-to-face therapy, we developed a low active and a relatively active variant of the two web-based CBT formats. Low active patients will start with a graded activity program early in therapy. Relatively active patients will first learn to spread their activities more evenly before starting the graded activity program. Following Stulemeijer [22] we do not expect different treatment outcomes for low or relatively active patients.

#### Web-based CBT—protocol driven feedback

Patients following web-based CBT with *protocol driven feedback* will be asked by the therapist to report on their progress according to a schedule set by the therapist. The therapist asks the patient to email at least weekly in the first four weeks and once every two weeks in the next eight weeks. After this period the therapist will propose a schedule dependent on the progress being made. We expect this will likely be once every two or three weeks until the end of the program. Therapists will send reminders if patients do not follow the schedule. Patients can book chat sessions with their therapists. Phone support will only be provided when needed urgently.

#### Web-based CBT—support on demand

Patients who will follow the web-based CBT with *support on demand* will only receive feedback if they ask for it. Patients will not receive any reminders from the therapist if they do not report on their progress via email.

#### Training and supervision of therapists

The therapists delivering the web-based CBT are psychologists and cognitive behavioural therapists who are trained and experienced in delivering CBT for CFS. They will receive weekly group supervision regarding the web-based CBT. All therapists received training to improve their online communication skills with patients. The therapist will aim to write the emails in such a way that it motivates patients to follow the instructions of the intervention.

#### Outcomes

All outcome measures are listed in Table 3. See Fig. 2 for a schedule of enrolment, interventions and assessments.

**Table 3 Tab3:** Outcome measures

	*Instruments*
Primary outcome measure	
Fatigue severity	Checklist Individual Strength, (CIS) subscale fatigue severity
Secondary outcome measures	
Level of disabilities	Sickness Impact Profile-8, (SIP8) total score
Physical functioning	Medical Outcomes Survey Short Form-36, (SF-36) subscale physical functioning
Psychological distress	Symptom Checklist 90items, (SCL-90) total score
Clinical significant improvement in fatigue	Checklist Individual Strength, (CIS) subscale fatigue severity < 35 and a reliable change index > 1.96

**Fig. 2 Fig2:**
[figure not shown]
Schedule of enrolment, interventions, and assessments

#### Primary outcome measure

Fatigue severity will be assessed with the subscale fatigue severity of Checklist Individual Strength [23]. This subscale consists of eight items assessing fatigue severity over the past two weeks. Scores range between eight (*no fatigue*) and 56 (*severe fatigue*). The cut-off score for severe fatigue is 35. This is two standard deviations above the mean of healthy controls [24]. The CIS is a reliable and valid instrument for the assessment of fatigue in CFS patients [23–25]. The Cronbach's alpha reliability coefficient for the subscale fatigue severity is .88 [23]. This outcome measure and cut-off point was also used in previous trials assessing the efficacy of a minimal intervention for CFS [26].

#### Secondary outcome measures

Level of disability will be measured with the total score of the Sickness Impact Profile (SIP8) [25]. The SIP8 assesses functional disability on the following eight domains: ambulation, home management, mobility, alertness behaviour, sleep and rest, work, social interactions, and recreation and pastimes. A weighted total score is computed from the scores on the eight subscales [12, 27]. This widely used measure has good reliability [27] and validity [5, 11].

Physical functioning will be assessed with the Medical Outcomes Survey Short Form-36 (SF-36) [28]. The subscale ‘physical functioning’ will be used. Scores on both scales range from 0 (maximum limitations) to 100 (no limitations). The SF-36 is a reliable and valid instrument to assess self-reported health status in CFS patients [28, 29].

Psychological distress will be assessed with the total score of the Symptom Checklist 90 (SCL-90) [30]. In total 90 items are answered on a five-point Likert scale. Total scores range from 90 to 450, with higher scores being indicative of more psychological distress. This widely used measure has good reliability and discriminating validity [31].

Clinical significant improvement in fatigue is defined as a reliable change index > 1.96 [32] and a score of < 35 on the CIS ‘fatigue severity’ subscale at second assessment.

#### Other study parameters

Based on the CBT for CFS model several fatigue related behaviours and cognitions will be assessed [33, 34]. The therapist will register invested therapist time for each patient. Actigraphy will be used to assess the level of physical activity. The actometer has been shown to be a reliable and valid instrument for the assessment of physical activity in CFS [18].

The presence of psychiatric disorders will be assessed using a structured diagnostic interview, the Mini International Neuropsychiatric Interview (MINI) screen test [19].

#### Adverse events

Adverse events will be assessed six months post randomization. Patients will be asked if they experienced new symptoms or an increase of existing symptoms during therapy or wait period. Patients who have received treatment will be asked if therapy in their opinion had negative side effects. Previous treatment studies have shown that regular face-to-face CBT and guided self-instructions for CFS are safe [35, 36].

### Statistical analysis

To determine whether web-based CBT leads to a reduction of fatigue severity compared to a wait list condition ANCOVA will be used. The second assessment of the primary outcome measure fatigue severity is the dependent variable in this analysis, with baseline CIS score as covariate, and condition as fixed factor. In RCTs ANCOVA yields greater power than other statistical methods [37]. Analyses will be based on intention to treat. Multiple imputation using fully conditional specification will be used to handle missing observations. The number of imputations will be at least equal to the percentage of missing data of the outcome measure. The assumption is made that data are missing at random [38]. A priori contrasts will be defined for the factor condition comparing web-based CBT with *protocol driven feedback* versus wait list and *support on demand* versus waiting list. When statistical significant differences are found, a sensitivity analysis will be performed on the basis of different assumptions about the values of missing data.

For the secondary outcome measures disabilities, physical functioning, psychological distress and the proportion of patients with clinical significant improvement in fatigue severity, the same analysis will be repeated, but with the secondary outcome measures at the second assessment as dependent variable, and the scores of these measurements at baseline as covariate. Statistical significance will be assumed at p < 0.025 (.05 corrected for two comparisons: web-based CBT with protocol driven feedback versus waiting list and web-based CBT with support on demand versus wait list) for the analysis of the results with respect to the primary outcome measure fatigue and p < 0.05 for secondary outcome measures. We will use a chi-square test to determine if the proportion of patients with a clinical improvement outcome significantly differ between treatment arm and wait list condition. We will also use ANCOVA to explore possible differences between the two web-based CBT formats with fatigue severity as dependent variable, baseline score as covariate and condition as fixed factor. Mean therapist time needed per patient in each web-based CBT format will be compared with an independent samples *t*-test and using bootstrapping when the therapist times are too skewed.

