#### Study population

In total 240 patients will participate in the study. All patients are referred to the Expert Centre for Chronic Fatigue (ECCF), a tertiary treatment centre for chronic fatigue of the Radboud university medical center in the Netherlands. All patients will meet CDC consensus criteria for CFS [1, 2]. They will all be severely fatigued with a score 35 or higher on the subscale fatigue of the Checklist Individual Strength (CIS). According to the consensus criteria the fatigue must be associated with significant disabilities. The latter is operationalized as scoring 700 or higher on the Sickness Impact Profile 8 (SIP8 total score). The other inclusion criteria are described in Table 1. Patients will be (temporarily) excluded when engaged in a legal procedure concerning disability-related financial benefits or when participating in other research [17]. We will assess the presence of psychiatric disorders using the MINI and clinical assessment and exclude patients who do not meet the inclusion criteria of the CDC with respect to current psychiatric disorders and/or having a medical history with psychiatric disorders.

**Table 1 Tab1:** Inclusion and exclusion criteria

1) ≥ 18 years.	
2) Able to speak, read, and write Dutch.	
3) Able to use a computer and have access to Internet.	
4) CFS diagnosis according to the CDC consensus criteria:	[1, 2]
5) Severe fatigue is assessed with the subscale fatigue severity of the Checklist Individual Strength (CIS). Severe fatigue is operationalized as scoring ≥ 35.	[23]
6) Disabilities; Disability is assessed with the total score of the Sickness Impact Profile (SIP8). Severe disability is operationalized as a total score ≥ 700 on the SIP8.	[27, 41]
7) Given written informed consent.	
Exclusion criteria	
1) Engaged in a legal procedure concerning disability-related financial benefits.	
2) Participating in other CFS research.	

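### Clinically significant improvement is given two analyses with no order between them, and the ANCOVA adjusts for a baseline value that is the same for every patient

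*Protocol article*

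**What the plan says.** All references are to the protocol article.

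- **Outcome.** Table 3 and Secondary outcome measures define clinically significant improvement by two conditions that must both hold: a reliable change index above 1.96 and "a score of < 35 on the CIS ‘fatigue severity’ subscale at second assessment".
- **Entry.** Under Study population, "They will all be severely fatigued with a score 35 or higher" on the CIS fatigue subscale. Table 1 repeats the threshold: "Severe fatigue is operationalized as scoring ≥ 35".
- **First analysis.** The Statistical analysis section lists the secondary outcomes, "and the proportion of patients with clinical significant improvement in fatigue severity, the same analysis will be repeated". That analysis is the ANCOVA of the primary outcome, with the secondary measure at the second assessment as dependent variable "and the scores of these measurements at baseline as covariate".
- **Second analysis.** Two sentences later in the same paragraph: "We will use a chi-square test to determine if the proportion of patients with a clinical improvement outcome significantly differ", each treatment arm being set against wait list.
- **Missing data.** Analyses follow intention to treat, and "Multiple imputation using fully conditional specification will be used to handle missing observations". No exception is made for this outcome.

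No sentence says that one of the two analyses replaces the other.

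**The concern.** One outcome has two tests and no rule for choosing between them. Read literally, the first cannot be applied: it adjusts for the baseline value of a variable that has only one value at baseline. It is also a linear model for a yes/no outcome. The second can be applied, but it leaves out baseline fatigue. Yet the same section justifies ANCOVA by its greater power, and the sample size section relies on that adjustment.

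The outcome is a named secondary outcome and part of the second hypothesis in the Background. If the covariate is read more generously as the baseline CIS score, both tests can be run and can give different answers. The choice between them would then be open after the data are seen.

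**Working it through.** **1. Baseline value of the outcome.** Improvement equals 1 only if the reliable change index exceeds 1.96 and the CIS score is below 35. At baseline there is no change yet, and entry requires a CIS score of 35 or more. Both conditions fail for all 240 patients, so the baseline value is 0 for everyone.

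**2. The ANCOVA as written.** The design has four columns: intercept, two treatment indicators and the baseline value. With the last column constant, its rank is 3, so the covariate effect cannot be estimated. Once the covariate is removed, what remains is a one-way ANOVA on a 0/1 variable, which is close to the chi-square test.

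**3. The generous reading.** If the covariate is the baseline CIS score, the model can be fitted, but it is then a baseline-adjusted linear model and a different test from the chi-square. In simulation (10% improvement on wait list and 25-30% on treatment; correlation 0.342 or 0.5; 68 or 80 per arm; 4,000 trials per setting) the two disagreed at p < 0.05 in 3-10% of trials. The figure was 7% at 25% improvement and correlation 0.342.

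**4. Is the chi-square sound?** With 80 per arm and no treatment effect, it rejected in 0.031 to 0.061 of 1,500 simulated trials per scenario; the Monte Carlo standard error is √(0.05 × 0.95 / 1500) ≈ 0.006. With 15% missing completely at random, 15 imputations and improvement derived from the imputed scores:

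| Pooling | Type I error | Power |
|---|---|---|
| Chi-square, D2 rule | 0.036 | 0.959 |
| Risk difference, Rubin's rules | 0.039 | 0.961 |

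Only a naive average of the chi-square statistics was slightly inflated (0.066).

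**5. The plan's own use of baseline adjustment.** The article gives no power figure for this outcome. Its primary figures reproduce. The pooled SD is √((12.1² + 8.7²)/2) = 10.54. A difference of 6.7, two-sided alpha 0.025 and power 0.95 then need 76 per arm by the noncentral t. Next, 76 × (1 − 0.342²) = 76 × 0.883 = 67.1, rounded up to 68, and 68/0.85 = 80.

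**6. What leaving out baseline costs.** Power at alpha 0.05, chi-square against logistic regression adjusted for baseline CIS, at equal sample size:

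| Scenario | Chi-square | Adjusted | Gain |
|---|---|---|---|
| 10% v 25%, r = 0.342, 68 per arm | 0.64 | 0.68 | 0.04 |
| 10% v 30%, r = 0.342, 68 per arm | 0.86 | 0.88 | 0.02 |
| 10% v 25%, r = 0.5, 68 per arm | 0.65 | 0.72 | 0.07 |
| 10% v 30%, r = 0.5, 68 per arm | 0.86 | 0.90 | 0.04 |
| Difference 6.7, SDs 12.1 and 8.7, r = 0.342, 80 per arm | 0.971-0.985 | 0.975-0.987 | 0.001-0.005 |

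A closed-form calculation for the first row gives 0.636 for the chi-square. A separate simulation put the adjusted power in the first and third rows at 0.67 and 0.70.

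Inputs from the article: correlation 0.342, the difference and SDs, 68 and 80 per arm, 15% drop-out. Assumptions: 10% on wait list; correlation 0.5; and, for the last row, baseline mean 46-50 with SD 5-6, wait-list mean 42-46 at the second assessment, and a reliable change threshold built from the stated alpha of 0.88 (1.96 × √2 × SD × √0.12, or 4.8 points at SD 5). The 25-30% is the Background figure for fatigue within normal limits after guided self-instruction, a related but not identical outcome.

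**The case against.** The strongest reply is that the specific sentence governs the general one. The ANCOVA sentence lists all secondary outcomes together, and the chi-square sentence then says what is done with the proportion. On the literal reading the ANCOVA collapses almost to the chi-square, so little is in conflict. On the other reading, Table 3 names the CIS subscale as the instrument for this outcome, so the baseline score could mean baseline CIS, and the model can be fitted. An unadjusted chi-square is valid in a randomised comparison, and adjusting it is a matter of efficiency.

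Much of this stands. The chi-square may well be the intended test, and it is sound. But the text does not say that it replaces the ANCOVA, and neither reading leaves a single stated analysis. Either one of the two cannot be estimated as written, or there are two different tests. The objections to being unable to fit the model and to having a choice of tests belong to different readings and should not be added together.

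Two stronger inferences are tempting and should not be drawn.

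- A reader might infer that a chi-square test cannot be used with multiple imputation and so falls back on completers. Nothing in the article limits this outcome to completers. Improvement can be derived in each imputed data set and the test or the risk difference pooled. A pooling rule is also a detail that an article may leave to its analysis plan.
- A reader might compare a chi-square at 68 per arm with an adjusted analysis at 80 and infer a large loss. That mixes sample size with choice of test: at 10% v 25%, the chi-square alone moves from 0.636 to 0.708 between those sizes.

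**Conclusion.** The point holds as a contradiction within one paragraph. A binary secondary outcome has two analyses with no precedence, and the ANCOVA, taken as written, adjusts for a constant. The first part follows from the text and the second from the entry criterion and the outcome definition; neither depends on simulation.

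The statistical cost is small. At equal sample size and the article's correlation of 0.342, baseline adjustment adds about 2 to 4 percentage points of power under the assumed 10% on wait list and 25-30% on treatment. It adds under 1 point in the scenarios built on the article's expected difference and SDs. Larger gains need a correlation that the article does not report.

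Only this secondary outcome is affected. The primary analysis, its alpha and the 76, 68 and 80 per arm are unchanged. It should be fixed, but it does not threaten the trial's main conclusion.

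**What to change.** Take clinically significant improvement out of the list in the ANCOVA sentence, delete the chi-square sentence, and put one rule in their place:

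- In each imputed data set, derive improvement from the observed or imputed CIS score at the second assessment.
- Fit a logistic regression with condition and baseline CIS score.
- Pool the two contrasts versus wait list by Rubin's rules and report them with confidence intervals.

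This keeps the baseline adjustment, fits the stated intention-to-treat and imputation approach, and gives an estimate as well as a test. If the sponsor prefers the chi-square, naming it as the only analysis would also end the contradiction, at the small loss of power shown above. The change is wording in one section. It needs no new data and leaves the sample size as it is.

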In the first format, patients are asked by their therapist to report on their progress by email according to a schedule. In response, the therapist offers feedback. This format is named *protocol driven feedback*. Asking patients to email regularly and providing regular feedback according to a fixed schedule makes online CBT time consuming for therapists, possibly without increasing its efficacy. Patients may also report on their progress with respect to parts of the web-based CBT they do not need therapist input for. An alternative way of providing support is to tailor it to the needs of the patient and only give feedback when the patient asks for it. We assume that this will be more time efficient—i.e., requiring less therapist time to deliver, —than giving support according to the preset schedule. We named this second format of the web-based CBT *support on demand*. The efficacy of both web-based CBT interventions will be determined by comparing each web-based CBT format to a wait list control group with respect to its effect on the primary outcome measure: fatigue severity. Subsequently, we will determine if both forms of web-based therapy lead to a reduction of disability, improved physical functioning, less psychological distress and/or a higher proportion of patients with a clinically significant improvement in fatigue compared to a wait list condition. Furthermore, the effect on treatment outcome of how and when feedback is delivered to patients will be determined in an exploratory analysis by comparing the efficacy of the two web-based CBT formats with each other with respects to its effect on primary and secondary outcome measures. We will also compare therapists’ time needed to deliver the intervention. We hypothesize that:Fatigue severity will be significantly lower at second assessment following web-based CBT compared to the wait list control group.Patients who receive web-based CBT will report significantly less disabilities and psychological distress and significantly more often show clinical significant improvement in fatigue compared to the wait list control group.Patients who received *protocol driven feedback* web-based CBT will report a significantly larger decrease in fatigue severity, level of disability, psychological distress and report more often a clinical significant improvement than patients who received web-based CBT with *support on demand*.

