### Sample size calculation

Based on a previous study with guided self-instructions [11] we expect a mean difference on the CIS fatigue severity score between each web-based CBT format and the wait list condition of 6.7. The standard deviation in this study at second assessment was 12.1 in the treatment condition and 8.7 in the wait list condition. In order to answer the primary objective of this study to detect a difference of 6.7 points on the CIS fatigue between each of the web-based CBT formats and the wait list condition, assuming the same standard deviations as in the aforementioned study, with a two sided alpha of .025 and a, power of .95, 76 patients are needed in each of the three conditions at T1. This number is based on a *t*-test. Because an ANCOVA with baseline assessment as covariate will be used (which increases statistical power) this sample size has been multiplied with (1–0.342^2^) [39]. The correlation between the baseline CIS-fatigue score and the score at second assessment was 0.342 in the aforementioned study. After correction 68 patients with complete data per condition are needed. Assuming a drop-out rate of 15%, based on previous trials testing the guided self-instruction [11, 12] we will have to include 80 patients in each group to have 95% power to detect the expected difference of 6.7 points on the CIS fatigue between each of the CBT formats and the wait list condition.

In an exploratory analysis we will determine whether there is a difference in efficacy between web-based CBT with *protocol driven feedback* and web-based CBT with *support on demand*. On the basis of the calculated sample size of 68 patients with complete data per treatment arm, a power of .80 and a two sided significance level of 0.05 we will be able to detect a difference between both conditions that corresponds with an effect size (Cohen’s d) of 0.48 (moderate size effect size).

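### Holm's step-down would add power to the two primary contrasts at the same 5% familywise error as the fixed 0.025 rule; optionally, the uncorrected secondary tests need a stated status

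*Protocol article*

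**What the plan says.** The Statistical analysis section defines two a priori contrasts on fatigue severity, each web-based format against wait list, and sets the level for them: "Statistical significance will be assumed at p < 0.025 (.05 corrected for two comparisons". The same sentence continues "and p < 0.05 for secondary outcome measures". The secondary outcomes are disability, physical functioning, psychological distress and clinically significant improvement in fatigue. Under Study design, each format is compared with wait list on all of them. No gate behind the primary result is stated.

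Hypothesis 2 in the Background expects that patients given web-based CBT will "report significantly less disabilities and psychological distress and significantly more often show clinical significant improvement in fatigue" than wait-list controls. It does not name physical functioning. Only the comparison of the two formats with each other is labelled exploratory.

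The Sample size calculation uses the primary level: "with a two sided alpha of .025 and a, power of .95, 76 patients are needed in each of the three conditions at T1". It claims 95% power for the expected difference "between each of the CBT formats and the wait list condition".

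**The concern.** Under the fixed rule, a second contrast with p between 0.025 and 0.05 is declared negative even when the first has been rejected. Familywise control at 5% does not require this. The lost power matters most if one format works somewhat less well than the other, which is plausible because the two differ in therapist contact.

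The secondary rule raises a question of consistency. The reason given for correcting the primary outcome is that two formats are compared with wait list, and that reason applies equally to each secondary outcome. The Discussion ties a possible first-choice role for the treatment to an effect on disability as well as fatigue, and disability is a secondary outcome. The status of those tests is therefore worth fixing in words.

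**Working it through.** **Inputs**, all from the Sample size calculation: difference 6.7 points; SD 12.1 (treatment) and 8.7 (wait list); baseline correlation 0.342; two-sided 0.025 per contrast; 68 complete patients per arm; 15% drop-out.

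**1. The plan's own figures.** Root mean square SD = √((12.1² + 8.7²)/2) = √(222.10/2) = 10.54, so d = 6.7/10.54 = 0.636. The noncentral t gives 76 per arm for power 0.95. Then 76 × (1 − 0.342²) = 76 × 0.883 = 67.1, rounded up to 68, and 68/0.85 = 80. All three figures reproduce.

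**2. Power per contrast under the stated rule.** SE = √(222.10 × 0.883/68) = 1.698, and 6.7/1.698 = 3.945. Power = Φ(3.945 − 2.241) = 0.956 (noncentral t: 0.952).

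**3. Bonferroni against Holm.** The contrasts share the wait-list arm, so their correlation is 8.7²/(8.7² + 12.1²) = 75.69/222.10 = 0.341. One million simulated pairs of contrasts, normal approximation, 68 per arm:

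| True effects | Rule | Contrast 1 rejected | Contrast 2 rejected | Both | At least one |
|---|---|---|---|---|---|
| 6.7 and 6.7 | Bonferroni | 0.956 | 0.956 | 0.918 | 0.993 |
| | Holm | 0.974 | 0.974 | 0.954 | 0.993 |
| 6.7 and 5 (assumed) | Bonferroni | 0.956 | 0.758 | 0.737 | 0.978 |
| | Holm | 0.967 | 0.832 | 0.821 | 0.978 |
| 6.7 and 0 (assumed) | Bonferroni | 0.956 | 0.025 | – | – |
| | Holm | 0.956 | 0.048 | – | – |
| 0 and 0 | Bonferroni | 0.025 | 0.025 | 0.002 | 0.048 |
| | Holm | 0.026 | 0.026 | 0.004 | 0.048 |

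As a check, with equal effects the power per contrast must be the mean of the last two columns: (0.918 + 0.993)/2 = 0.956 and (0.954 + 0.993)/2 = 0.974. Simulating 20,000 whole trials with ANCOVA and robust standard errors gives a similar picture: 0.95 to 0.971 per contrast and 0.909 to 0.948 for both.

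Holm raises the false-positive rate of a null contrast beside an effective one from 0.025 to 0.048, which is still within the 5% bound.

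**4. Secondary tests.** There are 4 outcomes × 2 contrasts = 8 tests. Hypothesis 2 names 3 outcomes, hence 6 tests. Two-sided testing at 0.05 is assumed. The document gives no correlations between outcomes, so a range of 0 to 0.8 is assumed, with correlation 0.5 between contrasts for the shared arm. Chance of at least one false rejection when nothing works:

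| Set | Independent tests | Shared arm, outcome correlation 0 to 0.8 |
|---|---|---|
| One outcome, 2 tests | 1 − 0.95² = 0.098 | 0.091 |
| Hypothesis 2, 6 tests | 1 − 0.95⁶ = 0.265 | 0.25 to 0.17 |
| All 8 tests | 1 − 0.95⁸ = 0.337 | 0.32 to 0.20 |

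Counting only false benefits, independence gives 1 − 0.975⁶ = 0.141 and 1 − 0.975⁸ = 0.183. With the shared arm the figures are 13% to 9% and 17% to 10%. Carrying 0.025 over to all eight tests would bring each outcome to 0.046 but leave 0.17 to 0.11 overall (two-sided).

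**The case against.** Bonferroni is a legitimate choice. It controls the error strongly, yields matching 97.5% intervals, and has been paid for in the sample size. At the design effect the gain is about 2 points on top of 95%. All of this stands, and it makes the point an improvement rather than the repair of an error.

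A reader might infer that the promised 95% power is not delivered, because power to show both formats effective is about 92%. The text does not support that. The calculation is per contrast, its wording about each format is naturally read that way, and no success rule requires both contrasts to be significant.

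On the secondary outcomes a reader might infer that a false claim is likely, that eight tests carry hypothesis 2, or that one false positive would confirm it. None of these holds. Six tests carry it; roughly one in six to one in four (two-sided) is not likely, and about half of those errors would point to harm. The hypothesis joins its outcomes with a conjunction, so one significant result would not establish it. The 0.05 level is openly prespecified, unadjusted secondary testing is common, and an analysis plan that is not shown could add a gate. What remains is that the article corrects for two comparisons in one place and not in the other, without a reason and without calling the secondary tests supportive.

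**Conclusion.** The primary rule is valid and consistent with the sample size, but a better one is available at almost no cost. With 68 complete patients per arm, the planned SDs and both effects at 6.7, Holm raises power per contrast from about 0.956 to 0.974 and for both contrasts from about 0.92 to 0.95. The chance of at least one success does not change. The gain is larger where a format falls short of the design effect: from about 0.76 to 0.83 at an assumed 5 points. Holm's validity does not depend on the correlation between the contrasts; the power figures rest on the plan's SDs and baseline correlation.

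The secondary point is real but optional, since whether to correct secondary outcomes is a trade-off. Two-sided error is about 9% per outcome over its two contrasts, about 17–26% over the six tests of hypothesis 2, and about 20–34% over all eight. The upper ends assume independent tests, and a false benefit is about half as frequent.

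**What to change.** **Primary.** Replace the fixed 0.025 with Holm at two-sided familywise 0.05: the smaller of the two p values is tested at 0.025 and, only if it is rejected, the other at 0.05. The sample size stays as it is. The cost is in reporting: a contrast rejected with p between 0.025 and 0.05 has a 97.5% interval that includes zero, so the plan should say which intervals will be shown.

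**Secondary (optional).** The simplest course is to state that the secondary tests are supportive, report estimates with confidence intervals, and remove the word *significantly* from hypothesis 2. This is wording only.

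If formal secondary claims are wanted, use one procedure that controls error across both formats together. Holm applied separately within each format, behind that format's primary contrast, is not enough: it leaves about 6–9% secondary familywise error when both primary contrasts are rejected. Joint control would make secondary claims somewhat harder to reach.
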